# Multicenter, PrOspective, Randomized, Controlled Trial Comparing GenIcular Artery EmbOlization Using Embosphere Microspheres to Corticosteroid iNjections for the Treatment of Symptomatic Knee Osteoarthritis: MOTION Study Protocol Summary

**DOI:** 10.1007/s00270-025-03994-z

**Published:** 2025-03-06

**Keywords:** Knee osteoarthritis, Genicular artery embolization, Embosphere® microspheres

## Abstract

**Purpose:**

Corticosteroid injections are commonly used to treat symptomatic knee osteoarthritis; however, pain relief is usually transient. Genicular artery embolization (GAE) has shown promise as an effective minimally invasive intervention to alleviate symptomatic knee osteoarthritis. The MOTION study is being conducted to compare outcomes following GAE versus corticosteroid injection.

**Materials and Methods:**

This is an international, multicenter, randomized controlled investigational device exemption (IDE) study enrolling adults (≥ 21 years old) with symptomatic knee osteoarthritis (Kellgren–Lawrence grades 1–4) across ≥ 45 centers worldwide. Patients will be randomized 1:1 to receive GAE with Embosphere® Microspheres (Merit Medical Systems, Inc.) or corticosteroid injections. The primary efficacy measure is clinical success at 6 months, defined as ≥ 50% improvement in the Western Ontario and McMaster Universities Osteoarthritis Index (WOMAC) Pain Subscale. The primary safety measure is the proportion of patients free from treatment-related safety event(s) through 6-month post-index procedure (GAE or corticosteroid injection). Following the 6-month visit, patients in either cohort who do not achieve clinical success may crossover to the other study arm. Additional study measures will assess safety and efficacy outcomes throughout the 24-month follow-up period. The target sample size is 264 (132 per arm) and is based on the number of patients needed to confirm superior efficacy of GAE versus corticosteroid injections and non-inferiority with respect to safety. The overall study power is > 80%.

**Discussion:**

Findings from the MOTION study are expected to provide information on the magnitude of the therapeutic benefits associated with GAE versus standard of care over 24 months.

**Trial Registration:**

NCT05818150.

**Graphical Abstract:**

[figure not shown]

## Introduction

Knee osteoarthritis is a common degenerative condition that can result in debilitating pain. Recognized risk factors associated with the development of knee osteoarthritis include obesity, repetitive joint stress and trauma, advancing age, diabetes, and family history [1]. Over the last several decades, the incidence and prevalence of knee osteoarthritis have steadily increased. From 1990 to 2019, the prevalence of knee osteoarthritis has increased by 7.5% and the number of new cases has increased by 6.2% [2]. In 2020, 654.1 million adults ≥ 40 years of age were estimated to suffer from knee osteoarthritis globally [3]. As the risk factors associated with the development of knee osteoarthritis increase, the incidence and prevalence of the condition will continue to rise. The increasing clinical burden of knee osteoarthritis is also associated with a high economic burden throughout the world [4–6]. A retrospective claims-based study published in 2017 estimated that direct annual costs of knee osteoarthritis in the USA (e.g., treatment, medical visits) incurred by patients ranged from $5.7 to 15 billion [5].

Intra-articular corticosteroid injections are commonly used as the standard of care to alleviate pain associated with knee osteoarthritis; however, their use typically provides short-term relief (e.g., 4–6 weeks of benefit) [7]. Moreover, there is evidence to suggest that repeat corticosteroid injections may be associated with significant cartilage loss without meaningful long-term pain relief [8].

Within the past decade, genicular artery embolization (GAE) has emerged as a minimally invasive treatment helpful in reducing, or eliminating, the pain associated with knee osteoarthritis [9–15]. It has been hypothesized that “pruning” of the hypervascularity in the synovial tissues surrounding the knee joint can reduce inflammatory processes and provide pain relief. If confirmed, these have the potential to result in meaningful improvements in patients’ health-related quality-of-life [10, 12–14, 16–18].

Considerable evidence has demonstrated the clinical utility of GAE; however, most studies have focused on single patient cohorts or compared outcomes against sham procedures. The MOTION study has been designed to directly compare clinical outcomes of GAE versus standard of care intra-articular corticosteroid injections.

## Methods

### Study Design

The MOTION study is a prospective, multicenter, randomized, investigational device exemption study that is being conducted at up to 45 centers across Australia, Europe, New Zealand, North America, and South America. The study is sponsored by Merit Medical Systems, Inc. (South Jordan, UT, USA; Trial Registration: NCT05818150).

### Eligibility Criteria

Table 1 summarizes the full list of eligibility criteria. Patients with confirmed knee osteoarthritis who meet all of the general inclusion criteria and none of the general exclusion criteria will be randomized into one of two arms: the treatment arm (i.e., GAE) or the control arm (i.e., corticosteroid injection). Patients who are assigned to the treatment arm are screened to ensure that they meet all angiographic eligibility criteria (Table 1) before they can undergo GAE. Patients randomized to the treatment arm who do not meet the angiographic eligibility criteria are considered an angiographic screen failure and will be followed through discharge only. Any patient who is randomized into the study, but later found to have not met all eligibility criteria will remain in the study and complete all trial testing and follow-up requirements.

**Table 1 Tab1:** Key inclusion and exclusion criteria

*General inclusion criteria*
Provides written informed consent Age ≥ 21 years Mild to severe knee pain, defined as a WOMAC Pain score of ≥ 8 out of 20 (in the target knee) Pain refractory to conservative therapies (e.g., anti-inflammatory drugs, or physical therapy, or muscle strengthening, or intra-articular injections) for at least 90 days prior to enrollment/randomization Kellgren–Lawrence grade 1, 2, 3, or 4 on radiograph of the knee within 6 months of enrollment/randomization (of the target knee)
*General exclusion criteria*
Planned major surgical or endovascular procedures ≤ 30 days after the index procedure Advanced atherosclerosis Known history of rheumatoid or infectious arthritis Received corticosteroid injection(s) in the target knee ≤ 90 days prior to treatment following enrollment/randomization Prior knee replacement surgery of the target knee
*Angiographic inclusion criteria*
Patient has confirmed evidence of knee osteoarthritis, defined as an angiographic ‘blush’ pattern (radiographic) in one or more of the target genicular artery(ies) Patient requires ≤ 4 genicular arteries to be treated
*Angiographic exclusion criteria*
Patient has evidence of arterial occlusion precluding catheterization (e.g., inability to cross iliac or superficial femoral artery(ies) and gain access to the genicular arteries) Patient has total occlusion of the genicular arteries on the target knee

WOMAC, The Western Ontario and McMaster Universities Arthritis Index

### Compliance with Ethical Standards

This study complies with the 1964 Helsinki Declaration and its later amendments. Ethics approval has been granted by the local ethics committees for each center participating in the study.

### Study Cohorts

Patients with symptomatic Kellgren–Lawrence Grades 1–4 (i.e., mild to severe) knee osteoarthritis will be randomized 1:1 into the treatment arm (GAE) or control arm (corticosteroid injection).

All randomized patients who do not achieve clinical success at 6 months will have the opportunity to crossover to the other study arm (i.e., crossover from active control to treatment [CtT], crossover from treatment to active control [CtC]). Crossover may only be selected following completion of the 6-month follow-up visit and quality-of-life assessment. Crossover will not be allowed at any subsequent time points during the study.

### Study Procedures

#### Screening

Any patient presenting to the participating centers with symptomatic knee osteoarthritis will be evaluated for eligibility and participation in the study (Table 1). If the patient meets the general eligibility criteria and is willing to participate in the study, written informed consent will be obtained. No study-specific requirements will be performed prior to obtaining informed consent from the patient.

#### Enrollment and Randomization

The MOTION study will enroll 264 patients across up to 45 centers, with a maximum of 15 centers allowed to be outside of the USA. Enrollment will not exceed 20% of total study population at any one center.

Patients will be randomized (1:1) to GAE or corticosteroid injection following confirmation that all eligibility criteria are met (Table 1).

#### Intervention

##### Treatment Arm

For patients randomized to the treatment arm (GAE), a baseline angiogram will be obtained to determine final eligibility prior to inserting the embolic agent into the vasculature.

An intra-arterial sheath will be placed via femoral access (ipsilateral or contralateral) for the GAE procedure. Radial and pedal access are not permitted in this trial. Prior to treatment with the embolic agent (Embosphere® Microspheres, 100–300 µm; Merit Medical Systems, Inc.), angiography will be performed according to standard of care at each participating center and in accordance with requirements from the core laboratory, to confirm the presence of hyperemia (i.e., ‘blush’ pattern, Fig. 1) within the synovial tissues surrounding the affected knee joint in accordance with the angiographic criteria (Table 1). If confirmed, the genicular artery(ies) will be assessed to identify culprit vessels contributing to the hypervascularity of the synovial tissue in the region of the knee joint.

**Fig. 1 Fig1:**
[figure not shown]
Genicular artery angiogram demonstrating “contrast blush” denoting hypervascularity (white arrow)

Under fluoroscopic guidance, the embolic agent will be injected with attention to avoid reflux and non-target embolization until adequate pruning of the hypervascularity is achieved (i.e., cessation of blood flow). Embolization will target small caliber distal vessels while maintaining patency of the larger main genicular artery. A maximum of four target vessels may be treated.

A final lower extremity angiogram will be performed to confirm success of the embolization procedure and determine if there are any associated complications. The patient will be discharged in accordance with each institution’s standard of care. Patients may be prescribed pain medications to treat post-procedure pain (e.g., non-steroidal anti-inflammatory drugs and/or other analgesics) according to the physician’s discretion. Medications prescribed to the patient will be documented in the case report form.

Patients who undergo GAE cannot receive concomitant treatment with a corticosteroid injection to manage procedural pain and inflammation.

##### Control Arm

For patients randomized to the control arm, the corticosteroid administered will be selected based on the standard practice and availability within the region of practice and limited to 40 mg of either triamcinolone or methylprednisolone. Both are long-acting steroids commonly used in the knee and a 40 mg dose has demonstrated activity out to 24 weeks [19, 20]. Only local topical or subcutaneous anesthetic may be used to manage local discomfort associated with the injection site procedure. Intra-articular steroid injections are not recommended more frequently than every 6 months, and patients are strongly discouraged from repeat injections at intervals less than every 6 months. Reintervention, including repeat injection, prior to the 6-month primary endpoint is considered a treatment failure per protocol.

The steroid will be injected into the joint cavity according to the physician’s discretion utilizing aspiration technique of synovial fluid or via ultrasound imaging to confirm presence within the joint cavity.

### Primary Outcome Measures

The primary efficacy outcome measure is the proportion of patients achieving clinical success at 6 months (180 days), defined as ≥ 50% improvement in the Western Ontario and McMaster Universities Osteoarthritis Index (WOMAC) Pain Subscale from baseline without the need for additional intervention (i.e., rescue treatment for inadequate pain relief such as intra-articular steroid injection or other interventions, exclusive of vascular intervention such as GAE).

The primary safety outcome is the freedom from treatment-related safety events through 6 months (180 days) following the index procedure.

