### Statistical Analysis

The proportion of the patients in the treatment and control arms achieving clinical success at 6 months will be compared. The hypothesis that treatment (GAE) is superior to control (corticosteroid injection). The number of patients needed to assess clinical success at 6 months was determined using a two-group Chi-square test based on the following assumptions: a clinical success rate of 65% for the treatment arm [12, 16] and a 40% clinical success rate for the control arm [8, 20, 21].

For the safety endpoint, treatment is hypothesized to be noninferior to control. The number of patients needed to assess the primary safety outcome was based on the following assumptions: (1) event-free safety rate of 95% in the treatment arm [11–14, 16, 22–24]; (2) event-free safety rate of 95% in the control arm [8]; (3) non-inferiority margin of 10%; (4) one-sided alpha of 0.025; (5) 85% statistical power; and (6) 15% attrition rate.

A required sample size of 264 patients (132 per arm) inclusive of a 15% attrition was determined. The overall study power is > 80%.

For purposes of endpoint determinations, the intent-to-treat (ITT) analysis set will include all randomized patients in both arms, and the modified ITT (mITT) analysis set will include all ITT patients who receive treatment and exclude patients that failed angiographic screening. The mITT analysis set will be used to evaluate the primary efficacy and safety outcome measures.

Continuous study measures will be summarized using descriptive statistics (mean, standard deviation, median, minimum, and maximum). Categorical or binary outcomes will be summarized using percentage with confidence intervals as appropriate.

Kaplan–Meier plots will be used to summarize time-to-event data. Continuous variables will be evaluated with independent t-tests. The threshold for statistical significance is *p* < 0.05.

Outcomes of crossover patients will be reported on a mITT basis and analyzed as separate populations (CtT and CtC).

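### The Control Arm text and the primary outcome definition conflict on scoring reintervention before 6 months; on the plain reading, repeat GAE and repeat injection are scored differently

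*Protocol article*

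**What the plan says.** The article addresses reintervention before the primary endpoint in two places.

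- **Primary Outcome Measures.** Success at 6 months (180 days) needs at least 50% improvement in WOMAC Pain and no additional intervention. The parenthesis defining that term reads "rescue treatment for inadequate pain relief such as intra-articular steroid injection or other interventions, exclusive of vascular intervention such as GAE". It applies to both arms.
- **Study Procedures, Control Arm.** "Reintervention, including repeat injection, prior to the 6-month primary endpoint is considered a treatment failure per protocol." The sentence stands under the control heading, but its first word is general.

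Three other places bear on the point.

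- **Treatment Arm** (text after Fig. 1). "Patients who undergo GAE cannot receive concomitant treatment with a corticosteroid injection to manage procedural pain and inflammation." This section neither scores a repeat embolization as failure nor prohibits one.
- **Study Cohorts.** "Crossover may only be selected following completion of the 6-month follow-up visit and quality-of-life assessment."
- **Statistical Analysis.** Efficacy is a superiority comparison planned on "a clinical success rate of 65% for the treatment arm" and a "40% clinical success rate for the control arm".

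**The concern.** Retreatment before the endpoint is evidence that the first treatment did not give adequate relief. An endpoint that requires success without further intervention therefore has to say which interventions void it, and say so in the same way for both arms.

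Here one section treats reintervention as failure. Another removes a class of intervention from the failure rule, and the example it names is the investigational procedure. If both are applied as written, repeating the assigned procedure ends the chance of success in the control arm but not in the GAE arm. If the Control Arm sentence is meant for both arms, the two sections contradict each other on repeat GAE.

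At stake is who counts as a success on the primary superiority endpoint of an investigational device exemption trial. If the choice is made after data are seen, it can look data-driven.

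**Working it through.** **1. The plan's own figure.** The stated size is 264 (132 per arm). The safety assumptions are an "event-free safety rate of 95% in the treatment arm", an "event-free safety rate of 95% in the control arm", a 10-point margin, one-sided alpha 0.025, power 85% and attrition 15%. The Farrington-Manning formula, with rates restricted to the margin under the null, is

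n = [(1.960 × √V0 + 1.036 × √V1) / 0.10]²

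- Restricted rates: 0.8703 and 0.9703, so V0 = 0.8703 × 0.1297 + 0.9703 × 0.0297 = 0.1417.
- V1 = 2 × 0.95 × 0.05 = 0.095.
- n = 111.7, rounded up to 112 per arm; 112 / 0.85 = 131.8, rounded up to 132.

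This matches. Efficacy power at 112 per arm (65% v 40%, chi-square, taken as two-sided 0.05) is 96.7%, and 0.85 × 0.967 = 0.82 agrees with the stated overall power above 80%. The endpoint wording enters none of this, so N does not depend on the point.

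**2. Scoring by event before 6 months.**

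| Event | Primary Outcome Measures, plain reading | Control Arm sentence |
|---|---|---|
| Repeat injection, control patient | Failure | Failure |
| Rescue steroid injection, GAE patient | Failure | Failure if general; silent if control-only |
| Repeat GAE, GAE patient | Can be success | Failure if general; silent if control-only |
| Off-protocol GAE, control patient | Can be success | Failure, if it counts as reintervention |

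Row 2 shows that steroid rescue voids success in both arms. Row 3 is either an arm difference or a contradiction, depending on how far the Control Arm sentence reaches. Row 4 is a conflict that would favour control.

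**3. Crossover does not explain the exemption.** Crossover opens only after the 6-month visit, so crossover GAE falls after the endpoint has been assessed.

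**4. Size (assumptions).** The article gives no rate of repeat GAE and no success rate after it. Compared with scoring repeats as failures, the gain in the GAE rate is (repeat rate) × (share of retreated patients who then succeed). With repeat rates of 2%, 5% and 10%, and the planned whole-arm 65% borrowed for that share:

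- 0.02 × 0.65 = 0.013 (1.3 points)
- 0.05 × 0.65 = 0.0325 (3.3 points)
- 0.10 × 0.65 = 0.065 (6.5 points)

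The planned difference is 65 − 40 = 25 points. Off-protocol GAE in control patients would add to the control rate by the same formula, so the net effect is the difference between the two products. Equal products would cancel.

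**5. Consequence if only the GAE arm is affected.** Exact binomial enumeration of the pooled chi-square test, 112 evaluable per arm, control 40%, two-sided 0.05:

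| Points added to GAE | Chance of a false result favouring GAE, strict success 40% in both arms | Power under an equal rule, if the planned 65% includes these patients |
|---|---|---|
| 0 | 2.4% | 96.8% |
| 1.3 | 3.8% | 95.0% |
| 3.3 | 7.1% | 91.1% |
| 6.5 | 16.5% | 80.2% |

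**The case against.** **The exemption can be read another way.** It may mean only that GAE is not among the rescue options before 6 months, rather than that a repeat GAE leaves success intact. That fits the crossover rule and the data collection schedule (Table 2), which has a single Day 0 index procedure; nothing in the article provides for a second embolization. This stands as a possible intention. It is not what the sentence says, and the article does not prohibit a repeat.

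**The Control Arm sentence may be general.** If so, repeat GAE is already a failure and there is no scoring bias once that sentence governs. This also stands, but it turns the problem into a contradiction with the endpoint definition. Either way the two sections need reconciling.

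**The full protocol may settle it.** The article is a condensation. However, the point rests on two statements the article does make, not on something it leaves out.

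**A reader might infer that retreatment is penalised in the control arm only, or that the endpoint is biased towards GAE.** The text does not support either. Steroid rescue also voids success for GAE patients, and the exemption names no arm, so off-protocol GAE in a control patient would favour control. Without event frequencies the net direction is unknown.

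**The sizes have no source.** The 2% to 10% range is assumed, and 65% is the planned rate for the whole arm, not for patients retreated because relief was inadequate. This objection stands in full: the figures are illustrations.

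**Conclusion.** The conflict is real. The failure rule under Control Arm and the exemption in the endpoint definition cannot both apply as written without either scoring repeats of the assigned procedure differently by arm or contradicting each other on repeat GAE. The difference is confined to that kind of retreatment and to off-protocol GAE in control patients.

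Under the assumed range, the addition to the GAE rate is 1.3 to 6.5 points. If repeat GAE before day 180 is rare, the numerical effect is small; if off-protocol GAE occurs in the control arm, it offsets the effect or reverses it. The false-positive and power figures hold only if no such offset exists and 112 patients per arm are evaluable. What does not depend on any rate is that the primary endpoint has no single scoring rule for these patients.

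**What to change.** Reconcile the Control Arm and Primary Outcome Measures sections into one endpoint-scoring statement on reintervention before 6 months. It should apply equally to both arms and say expressly how repeat GAE, repeat injection and off-protocol GAE in a control patient are scored. Carry the same derivation into the analysis plan, settle it before outcomes are analysed, and tabulate reinterventions before the endpoint by type and arm.

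This concerns scoring only; it takes no position on whether retreatment is given. The cost is one sentence, the matching derivation and one table, with no change to the 264 patients. The downside is that the GAE success rate may come out slightly less favourable.

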### Additional Outcome Measures

Secondary outcome measures will include: the number of patients who achieve clinical success at 3, 12, and 24 months; patient rating of pain at baseline, 3, 6, 12, and 24 months as assessed using the Numerical Rating Scale (NRS); the number of patients who achieve ≥ 50% reduction in the mean NRS pain score at 3, 6, 12, and 24 months. Additional secondary outcome measures will include assessments of technical success (defined as successful procedural occlusion of the target genicular arteries confirmed fluoroscopically by the treating physician), device-related and serious adverse device effects through 24 months, in addition to symptom-related changes throughout the study period. Exploratory endpoints will include, as available, the number of patients that progress to partial or total knee replacement and outcomes in any crossover patients will also be described.

